### Data collection methods

2.7

Baseline status of physical status of the participants and their baseline findings of their esophageal carcinoma, endoscopy, computed tomography (CT), and positron emission tomography CT (PET-CT), are evaluated before the treatment begins. The patients hospitalize into our hospital just before the start date of the treatment; subsequently, physical status, and laboratory data are regularly checked by the physicians in charge of their hospital care. The status of tumor is re-evaluated using endoscopy, CT, and PET-CT 1 month after the treatment, and chemotherapeutic effect is diagnosed according to RECIST ver 1.1. If unresectable factors are not being found in the reevaluation of tumor, the patients will undergo curative surgery for their esophageal carcinoma. The pathological diagnosis of resected specimens is determined by expert pathologists according to Japanese Classification of Esophageal Cancer, 11th Edition.^[11,12]^ After the surgery, the patients undergo regular follow-up using endoscopy, CT, and PET-CT. The collected data are submitted to data management center by physicians in charge of the hospital care using specific case record forms. The data are managed by the responsible doctor. To protect personal information, the collected information is saved with encrypting the personal data under offline. Oncological outcomes will be investigated at the end of the trial and 3 years later.

### Statistical methods

2.8

1.***Population to be analyzed.*** All subjects enrolled in the present study (full analysis set [FAS]), excluding patients with serious violations (including serious protocol deviations, violations of inclusion/exclusion criteria, and violations of prohibited concomitant medication/therapy) from FAS (per protocol set).2.***Primary endpoint.*** The primary endpoint is the rate of good pathological therapeutic effect. Primary tumor samples of ESCC will be obtained from patients who have undergone curative esophagectomy after preoperative adjuvant chemotherapy. The grade of the pathological therapeutic effect will be evaluated. Clinical diagnosis according to the 11^th^ edition of the Japanese Classification of Esophageal Cancer^[11,12]^3.***Secondary endpoints.*** The secondary endpoints are the objective response rate (ORR), safety of preoperative adjuvant chemotherapy, recurrence-free survival (RFS), and overall survival (OS). RFS and OS will both be calculated as the time from surgery to first recurrence and all-cause death, respectively.a.***ORR.*** Local responses will be evaluated using CT and PET-CT images obtained after preoperative adjuvant chemotherapy in accordance with the 11^th^ edition of the Japanese Classification of Esophageal Cancer.^[11,12]^b.***Safety: Treatment-related adverse event.*** The safety of preoperative adjuvant chemotherapy will be assessed according to CTCAE version 5.0.c.***RFS curve.*** The Kaplan-Meier method will be used to estimate the RFS curve and calculate 3-year RFS and 95% confidence intervals.d.***OS curve.*** The Kaplan-Meier method will be used to estimate the OS curve, and annual and 3-year OS rates and their 95% confidence intervals will be calculated.4.***Ethics*** The present trial was approved by the Ethics Committee of Kyoto Prefectural University of Medicine, Kyoto, Japan (Approval number: CRB5180001, 30/Aug/2019). This trial is subject to the supervision and management of the Ethics Committee. If the protocol modifications are needed, the revised protocol must be approved again by CRB. The physicians with sufficient knowledge regarding the present trial obtain informed consent or assent from trial participants using the specific explanation sheet.5.***Trial status*** Recruitment started in November 2019, with the final follow-up planned for March 2029. One subject has been enrolled since October 21^st^, 2020.

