**Patients and methods::**

Between 56 and 59 patients aged between 20 and 74 years with clinically diagnosed Stage II or Stage III ESCC will be enrolled. Eligible patients will receive preoperative adjuvant chemotherapy, 2 cycles of combination therapy with cisplatin, 5-fluorouracil, and tranilast. Recruitment started in November 2019, with the final follow-up being planned for March 2029. One subject has been enrolled since October 21^st^, 2020. The pathological therapeutic effect is the primary endpoint. The objective response rate, safety of preoperative adjuvant chemotherapy, recurrence-free survival (RFS), and overall survival (OS) are the secondary endpoints. RFS and OS will be calculated as the time from surgery to first recurrence and all-cause death, respectively.

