### Rationale for setting the target population size

2.6

Between 56 and 59 patients will be enrolled in the present study. An analysis of historical control data from patients who previously received conventional preoperative adjuvant chemotherapy (5-FU/CDDP) in our institute showed good pathological therapeutic effects (tumor regression grade 2 or 3 according to the 11^th^ edition of the Japanese Classification of Esophageal Cancer^[11,12]^) in 19% of patients. Therefore, expected and threshold rates are 34% and 19%, respectively. Under these conditions, 48 subjects will be required based on the assumption of a 1-sided alpha error of 0.05 and beta error of 0.2. In consideration of dropouts, the sample size is set at 50 patients for the phase II trial. Between 9 and 15 patients will be required to establish MTD (phase I trial). Data from 3 of these patients with established MTD will be used for the phase II trial. Therefore, the total sample size has been set at 56 to 59 patients in the present trial.

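### RFS as defined does not count death as an event, and starting RFS and OS at surgery leaves patients who are never resected out of both curves

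*Protocol article*

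**What the plan says.** The event and the time origin are given twice, in almost the same words. Section 2.8 (Statistical methods, secondary endpoints) has "RFS and OS will both be calculated as the time from surgery to first recurrence and all-cause death, respectively", and the Abstract (Patients and methods) has "RFS and OS will be calculated as the time from surgery to first recurrence and all-cause death, respectively".

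The estimators, also in section 2.8, are "The Kaplan-Meier method will be used to estimate the RFS curve and calculate 3-year RFS and 95% confidence intervals" for RFS and "The Kaplan-Meier method will be used to estimate the OS curve, and annual and 3-year OS rates and their 95% confidence intervals will be calculated" for OS. No competing-risk method is named and no censoring rule is given.

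Surgery is not automatic. Section 2.7 (Data collection methods) says: "If unresectable factors are not being found in the reevaluation of tumor, the patients will undergo curative surgery for their esophageal carcinoma". That decision follows a re-staging: "The status of tumor is re-evaluated using endoscopy, CT, and PET-CT 1 month after the treatment". Section 2.5 places all of the tranilast in two 3-week cycles before that point.

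The first analysis population listed in section 2.8 is every enrolled subject, resected or not. The section does not say which population serves RFS and OS.

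**The concern.** There are two separate problems.

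**The RFS event.** The definition pairs RFS with recurrence and OS with death. A patient who dies after oesophagectomy without recurrence has no RFS event. In a Kaplan-Meier analysis that patient is censored at death, as if still able to recur later. The result is a recurrence-only curve carrying the name of recurrence-free survival.

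**The origin.** The treatment being tested ends before surgery, so reaching surgery is itself an outcome of treatment. A patient who dies, progresses or becomes unresectable beforehand has no time zero and cannot enter either curve. OS then describes survival among those resected, not among those given the regimen. Sections 2.3 and 2.5 plan a comparison with the institution's earlier patients. If resection rates differ between the two groups, curves that start at surgery compare differently selected patients.

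**Working it through.** **The plan's own figure.** The protocol gives no survival, non-resection or postoperative death rate, so there is no survival figure to reproduce. The one computable design figure is the sample size for the pathological endpoint, where "expected and threshold rates are 34% and 19%, respectively", with one-sided alpha 0.05 and beta 0.2 (section 2.6):

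n = [(1.645·√(0.19·0.81) + 0.842·√(0.34·0.66)) / 0.15]² ≈ 48.4, against the stated 48.

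It uses no survival input, so this point does not touch it.

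**RFS: effect of leaving out death.** Let S be the 3-year recurrence-only Kaplan-Meier estimate and d the net 3-year probability of death without recurrence (one minus the Kaplan-Meier estimate for that event, with recurrence censored). Both analyses remove a patient from the risk set at the same time. Without ties, therefore,

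RFS counting death = S × (1 − d).

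This is never above S, and it is below S once a death without recurrence occurs within 3 years while S is above zero. All values of S and d below are assumptions.

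| S (recurrence only) | d = 5% | d = 10% | d = 15% |
|---|---|---|---|
| 50% | 47.5% | 45.0% | 42.5% |
| 60% | 57.0% | 54.0% | 51.0% |
| 70% | 66.5% | 63.0% | 59.5% |

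At S = 60% the overstatement is 3, 6 and 9 points. Over the whole table it runs from 2.5 to 10.5 points.

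**OS: effect of origin and selection together.** Two effects pull in opposite directions.

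1. *Selection.* Leaving out unresected patients raises OS. Let u be the unresected fraction, and assume 3-year survival of 65% in resected and 20% in unresected patients. On one common clock, all-patient OS is (1 − u)·0.65 + u·0.20, which is 62.75% at u = 5% and 58.25% at u = 15%. The gap is 2.25 to 6.75 points.
2. *Clock.* Resected patients have, by definition, survived to surgery, and the surgery clock gives no credit for that time. Two 3-week cycles plus about 1 month is about 10 weeks. With a constant hazard after surgery, λ = −ln(0.65)/3 = 0.1436 per year, and 3 years from enrolment is 3 − 10/52 = 2.808 years from surgery. Resected patients' survival is then exp(−0.1436 × 2.808) = 66.8%.

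OS from enrolment in all patients is (1 − u)·0.668 + u·0.20:

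| u | OS from enrolment, all patients | OS from surgery, resected | Difference (points) |
|---|---|---|---|
| 2% | 65.9% | 65% | −0.9 |
| 5% | 64.5% | 65% | +0.5 |
| 10% | 62.1% | 65% | +2.9 |
| 15% | 59.8% | 65% | +5.2 |

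The two are equal at u = (0.668 − 0.65)/(0.668 − 0.20) ≈ 4%.

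Other assumed survival pairs (resected/unresected) behave alike. For u = 2, 5, 10 and 15%, 60%/10% gives −1.0, +0.6, +3.2 and +5.8 points, and 70%/10% gives −0.4, +1.5, +4.5 and +7.6 points. Ten weeks is close to a minimum, since surgery follows re-staging; a longer gap moves the break-even fraction up.

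**The case against.** The strongest reply is that this is a condensed article, that one compressed sentence defines two endpoints, and that the name recurrence-free survival suggests deaths were meant to count. Censoring of deaths is indeed inferred: no rule states it. But the event is stated, in two places and the same way, and a fuller document would have to contradict it for deaths to count. The RFS part stands.

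Surgery is also a reasonable origin for RFS, because recurrence presupposes resection. That stands, and RFS from surgery can remain if labelled as applying to resected patients.

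A reader might infer more than the text supports:

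- *Both curves are certainly too favourable.* This holds for RFS once a death without recurrence occurs. For OS the clock effect offsets the selection effect, and the sign depends on the unresected fraction.
- *The surgery origin contradicts the full analysis set.* Section 2.8 does not say that RFS and OS are estimated in all enrolled subjects. The text leaves unresected patients without a place in either curve; it does not promise them one.
- *Harm from the added drug would go unseen.* Postoperative deaths do count in OS. Preoperative toxicity falls under the separate CTCAE safety endpoint, the dose-limiting toxicity definition and the stopping rule in section 2.5. Preoperative failures are missing from these two curves, not from the trial.

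Finally, RFS and OS are secondary and described only by estimates with confidence intervals. With 50 patients and 65% survival, the 95% half-width is about 1.96·√(0.65·0.35/50) = 13 points, wider than any bias shown. That lowers the priority. It does not excuse a definition that can be corrected in a sentence.

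**Conclusion.** The point holds for secondary endpoints and should be corrected, but it does not threaten the trial's main conclusion.

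The RFS definition is wrong as written. Its direction of error is fixed, at 3 to 9 points in the 60% example, given net death without recurrence of 5 to 15%.

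The surgery origin makes OS conditional on resection and leaves out the preoperative failures of a preoperative treatment. Its net bias is not fixed in sign: about 0.5 to 5 points too favourable at 5 to 15% unresected under the 65%/20% assumption, and nil or reversed below about 4%. This rests on a constant hazard and a 10-week gap. Every survival, death and non-resection rate used is an assumption, because the protocol gives none.

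**What to change.** 1. Define the RFS event as first recurrence or death from any cause, whichever comes first, in section 2.8 and the Abstract. Keep surgery as the origin and label the result a resected-patient analysis.
2. Report OS from enrolment to death from any cause in all patients treated at the MTD. Keep OS from surgery as a supplementary resected-patient estimate.
3. Apply the same events, origin and population rule to the historical patients in any survival comparison.

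The cost is a few sentences and, probably, somewhat lower estimates. It is not only wording, though: section 2.7 describes follow-up only after surgery, so survival status for the few unresected patients must be confirmed as collected, or added. The article reports one subject enrolled, so at that stage the change could be made prospectively.

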### Study design

2.1

The present study is a single arm, open-label prospective intervention phase I/II trial.

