### Objectives

2.2

The purpose of the present study is to confirm the clinical safety and efficacy of the additional use of tranilast with conventional preoperative adjuvant chemotherapy (5-FU/CDDP) for patients with advanced ESCC in a phase I/II design.

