**Figure 1 F1:**
[figure not shown]
Establishing the maximum tolerated dose (MTD) of tranilast. Initially, 200 mg/day tranilast will be administered to the first 3 patients. If 2 cycles of combination therapy are successfully completed without dose-limiting toxicity (DLT), 300 mg/day tranilast will be administered to the next 3 patients. The dose of tranilast will gradually be increased up to 600 mg/day, and the appropriate MTD will be established. This study will be stopped when DLT occurs at 200 mg/day tranilast. Dose modifications are allowed when DLT occurs at 300 or 600 mg/day tranilast. DLT: grade 4 toxicity according to the Common Terminology Criteria for Adverse Events (CTCAE) version 5.0.

Two cycles of combination therapy with the established MTD of tranilast will then be given to 50 patients. Their data will be compared with historical control data from patients who previously received conventional preoperative adjuvant chemotherapy (5-FU/CDDP) in our institute. This clinical study will be stopped when grade 4 toxicity occurs at the MTD of tranilast in >5 patients.

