### Quality control and trial monitoring

2.9

Before the start of the trial, all researchers will receive special training to guarantee the quality of the study. The training includes how to select and exclude participants, how to implement interventions correctly, how to record case report forms in a standard way, how to assess outcomes and manage data. To improve the compliance of participants, investigators will provide health education, and fully respect the informed consent right of them. Raw data will be recorded in the case record form, and 2 data managers will input the data into the spreadsheet and recheck the data respectively. To ensure the objectivity of the data, the assessment and statistics will be blinded during the trial. The principle researcher will supervise the whole trial.

If adverse events or other unintended effects of the interventions occur, the clinicians in charge need to report the principle researcher immediately, and provide the patient with appropriate therapies for the events. The compensation for participants to adverse event caused by the intervention is provided under sufficient consideration. Monitoring of the trial qualities is performed every 2 months during the trial by the researcher in charge of it.

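### The safety endpoint is labelled as treatment-related adverse events, which in a single-arm, open-label trial rests on causality calls that no concurrent group can check; all-cause events should be tabulated first

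*Protocol article*

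**What the plan says.** Section 2.8 lists safety as a secondary endpoint. Item 3b is headed "Safety: Treatment-related adverse event", and the sentence under it reads "The safety of preoperative adjuvant chemotherapy will be assessed according to CTCAE version 5.0". The neighbouring items 3a (ORR), 3c (RFS curve) and 3d (OS curve) also put the measure in the heading and describe it underneath.

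Section 2.1 calls the study a "single arm, open-label prospective intervention phase I/II trial". Section 2.2 makes safety of adding tranilast to 5-FU/CDDP part of the trial's purpose, alongside efficacy.

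Other safety wording in the article has no relatedness term:
- Section 2.5 defines dose-limiting toxicity by severe toxicities of grade 4 or 5, and leaves out certain expected grade 4 reactions by type of event.
- Section 2.5, after Figure 1, stops the study when more than 5 patients have grade 4 toxicity at the MTD.
- Section 2.9 states: "If adverse events or other unintended effects of the interventions occur, the clinicians in charge need to report the principle researcher immediately".

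Of the 50 patients treated at the MTD, section 2.5 says: "Their data will be compared with historical control data from patients who previously received conventional preoperative adjuvant chemotherapy".

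**The concern.** A treatment-related endpoint puts a causality judgement between the event and the table. In a randomised trial a poor judgement can be noticed, because the all-cause rates in the two arms can be set against each other. Here there is one arm, treatment is open, and all patients receive all three drugs. If an event caused by the combination is called unrelated, it leaves the endpoint and nothing inside the trial would reveal that.

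Safety of the combination is a stated aim, so the reported safety result should depend as little as possible on a judgement that cannot be checked. The wording also leaves open what treatment means in item 3b: tranilast alone, or the whole preoperative regimen.

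**Working it through.** The article gives no figure for the safety endpoint, so there is none to reproduce. The check is a comparison of the passages, followed by the simple relation that shows which quantity is missing.

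**1. Is the relatedness qualifier a stated choice?** All four secondary items in section 2.8 carry the measure in the heading. Read the same way, the measure in 3b is the treatment-related adverse event. The sentence below it supplies a grading scale and does not widen the measure to all events. This is something the article states, not a detail left to a fuller document.

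**2. Is the qualifier used consistently?**
- Section 2.8, item 3b: qualifier present.
- Section 2.5, dose-limiting toxicity: no explicit qualifier; exclusions are by type of event.
- Section 2.5, stopping rule: no explicit qualifier.
- Section 2.9, event reporting: no explicit qualifier on adverse events. The same section later speaks of compensation for an adverse event that the intervention caused, so the article itself knows the distinction.

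Item 3b is thus the one place where the safety measure is explicitly narrowed.

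**3. Can the judgement be checked inside the trial?** Section 2.1 gives one open arm, and section 2.5 gives cisplatin, 5-FU and tranilast to everyone. There is no group without tranilast treated at the same time. Section 2.9 says that assessment and statistics will be blinded, but with a single open-label arm there is no allocation to conceal. That statement needs reconciling with section 2.1, and it does not supply the missing check.

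**4. What would the size depend on?** Let *p* be the true proportion of patients with a given event caused by the regimen, and *f* the fraction of those events judged related. The reported proportion of such events is

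reported = *p* × *f*.

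The documents give neither *p* nor *f*. Purely as an illustration, assume *p* = 0.15 in 50 patients and *f* between 0.6 and 1:
- *f* = 1: 50 × 0.15 = 7.5 patients, 15%.
- *f* = 0.6: 7.5 × 0.6 = 4.5 patients, 4.5 / 50 = 9%.

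The range runs from no loss at all to a loss of 6 percentage points, and both ends come from the assumptions. It shows the mechanism and does not estimate the effect in this trial.

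**5. Does anything else move?** No. The sample size in section 2.6 concerns the pathological response, so no sample size or error rate changes.

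**The case against.** The strongest reply is that a sub-heading is being over-read. The sentence under it, and the endpoint list in both section 2.8 and the abstract, refer to the safety of the preoperative chemotherapy without any filter. How events are collected, attributed and tabulated is normally set out in the full protocol or analysis plan, which are not shown. Related and all-cause rates also answer different questions, and all-cause counts include events due to the disease.

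Much of this stands, and it rules out several stronger readings that a reader might infer:

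- **That only related events will be counted.** The article does not say so, and does not say that other events go unrecorded. The label makes the related events the named endpoint and goes no further.
- **That the treating physicians judge causality.** No assessor is named. Section 2.7 has them submit the forms and section 2.9 has clinicians report events. Missing causality criteria are no fault in an article.
- **That unfiltered data already exist.** The sentence in section 2.9 can be read as treating adverse events as one kind of intervention effect, so all-cause capture is likely but not established.
- **That a historical safety comparison is compromised.** Section 2.3 ties the historical comparison to efficacy, and the only historical figure given is the 19% response rate in section 2.6. The broader sentence in section 2.5 names no safety comparison.
- **That physicians must separate tranilast from its partner drugs.** If treatment means the whole regimen, as the abstract and section 2.5 suggest, only the distinction between regimen and disease or other causes remains.
- **That the reported rate is certainly too low.** Unrelated events may also be judged related, so the net direction is not fixed.
- **That the stopping rule is weakened.** If the rule of more than 5 in 50 counted only related events, then at an assumed true grade 4 rate of 15% the chance of stopping would fall from 0.781 with all events counted to 0.499 with 75% counted. As written, the rule has no such filter, so these figures do not describe the plan.

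What the reply does not remove is the label itself, which is stated, narrower than the rest of the article, and not checkable within this design.

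**Conclusion.** The point holds as a cheap improvement. Item 3b names a relatedness-filtered safety endpoint, whereas the dose-limiting toxicity definition, the stopping rule and the event reporting carry no explicit relatedness qualifier. In a single-arm, open-label trial, events from the combination that are wrongly judged unrelated would drop out of the reported safety result without trace.

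The conclusion rests on reading the heading of 3b as the name of the measure, as its neighbours are read. The size of the effect cannot be derived from the documents. The rules that govern escalation and stopping are not shown to be affected.

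**What to change.** Restate item 3b as all adverse events during protocol treatment up to surgery, tabulated by CTCAE version 5.0 term and worst grade per patient, regardless of attribution. Show the treatment-related subset in a second table, and say that related means related to the cisplatin, 5-FU and tranilast regimen. If any safety comparison with the historical controls is made, base it on the all-cause figures.

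The cost is one sentence and one extra table. Headline frequencies will be somewhat higher and will include disease-related events, which the second table puts in context. The case record form must capture events regardless of attribution, if it does not already do so.
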